**Intervention Measures:**

**Engagement** is “the act of being occupied or involved with an external stimulus” and will be assessed in two ways: (1) Participation: Total number of sessions attended; longest streak of consecutive classes attended, per person. This will be recorded for both EUC and FoRKS participants throughout their scheduled intervention. (2) Self-report survey: Total scores on a modified Classroom Engagement Survey, administered approximately every 3 weeks to FoRKS participants during Extended Delivery Training. This structured questionnaire has 16 items that assess, over the prior 3 weeks, the participant’s: affective engagement (e.g., “I feel interested”); behavioral engagement (e.g., “I actively participate in class discussions”); cognitive engagement (e.g., “I go back over things that I don’t understand”); and disengagement (e.g., “I let my mind wander”).

**Participant Experience** will be assessed approximately every 3 weeks to FoRKS participants during Extended Delivery Training and include Likert scale questions regarding satisfaction with foods, class content, instructions, and technology. We will summarize Likert scale scores and use qualitative feedback to make intervention adjustments as the study progresses. Once, at the PT visit, subjects will be asked about any personal “costs” experienced during the FoRKS intervention.

1. **Statistical Considerations**

**Power and Sample Size.** We determined the sample size to ensure adequate power for testing the primary hypothesis on the effectiveness of the proposed FoRKS intervention on systolic blood pressure (SBP). Specifically, we hypothesize that in comparison to EUC, FoRKS participants will have lower SBP (-6.0 mm Hg) at PT. That a difference of 6 mm Hg is clinically meaningful is supported by a 2021 Lancet meta-analysis involving 48 randomized trials and 344,716 participants that showed a reduction of >5 mm Hg in SBP was associated with a 10% reduction in major CVD events regardless of baseline SBP.

To ensure we have adequate power to detect an effect on SBP, we plan to enroll 100 subjects for each treatment group (n=80 per group at PT assuming 20% attrition). Using a conservative estimate of the SD of 12 mm Hg, we estimate that 100 subjects per group (80 after attrition) will give us 88% power to detect a 6 mm Hg difference in SBP between the treatment groups, with a two-sided t-test at 0.05 significance level.

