We have not determined the target sample size based on the analytical power for the secondary outcome (HbA_1c_), because we cannot control how many subjects in our sample will have both HTN and DM2.

**Data management.** Assessment data will be directly entered into REDCap, a web-based secure relational data management system for research data. A data dictionary including each interview question and definition for each response will be generated and used to build the REDCap database. The database will include internal error checking algorithms to prevent erroneous data entry or missing data. EMR and biomarker data will be merged with other study data and stored as SAS data sets on secure servers with access limited to data analysts working on this study and those meeting requirements for data sharing (see Data Storage and Sharing document). Video data will be stored using IU’s enterprise instance of OneDrive, in a HIPAA compliant secure folder created by IU for sensitive data.

**Analytic Plan**. The primary analyses will be carried out following an intention-to-treat (ITT) principle. Per-protocol analyses will be performed secondarily as supplements to the ITT analyses.

**Primary Aim.** We will use the trial data to determine the effects of FoRKS intervention on SBP and, secondarily, glucose management. We will test the hypothesis that compared to EUC, FoRKS participants have lower mean SBP at PT. Among those with both HTN and DM2, we will secondarily examine FoRKS’ effect in lowering HbA_1c_. Mean SBP at PT will be compared between the two treatment groups using a t-test. Mean HbA_1c_ will be compared using the same test. A similar analysis will be performed at FU to determine the sustainability of intervention effects on both outcomes. The planned t-tests at the end of the intervention (PT) are to evaluate the effects of the full dose of the intervention and the sustainability of the intervention at FU. This said, in addition to the main analysis described above, we will use mixed-effect models to assess the time course of the intervention effects by modeling repeatedly measured BP (BL, 5wk, PT, and FU) and HbA_1c_ (BL, PT, FU); random subject effects will be included to account for the potential correlation among repeated measures contributed by the same subjects. These secondary analyses will allow us to control the effects of any participant characteristics that are not balanced.

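### The primary analysis is labelled intention-to-treat, but the t-test named for it uses only participants with a PT systolic pressure and sets aside the baseline and week-5 readings.

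*Protocol*

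**What the plan says.** All of this stands in the protocol's Statistical Considerations section.

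- **Principle.** Under Analytic Plan: "The primary analyses will be carried out following an intention-to-treat (ITT) principle". The next sentence adds "Per-protocol analyses will be performed secondarily as supplements to the ITT analyses".
- **Primary test.** Under Primary Aim: "Mean SBP at PT will be compared between the two treatment groups using a t-test". No baseline adjustment is mentioned. The stated purpose is: "The planned t-tests at the end of the intervention (PT) are to evaluate the effects of the full dose of the intervention".
- **Expected numbers.** Under Power and Sample Size, 100 per arm are enrolled, with "n=80 per group at PT assuming 20% attrition".
- **Repeated-measures model.** Under Primary Aim: "in addition to the main analysis described above, we will use mixed-effect models to assess the time course of the intervention effects". It covers BP at BL, week 5, PT and FU, includes random subject effects, and is described as secondary.

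Measures and Outcomes adds that the Omron BP is taken at BL, after the self-management classes (week 5), at PT and at FU. The 24-hour ambulatory BP (ABPM) is taken only at the Eligibility Visit (EV) and PT. Primary Aim does not say which of the two supplies the primary SBP.

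**The concern.** Intention-to-treat has two parts: analysing people in the arm to which they were randomised, and accounting for everyone randomised. The plan meets the first part. The named method does not meet the second, because a t-test of PT means, taken as written, has nothing to work with for a participant who has no PT reading.

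The plan itself expects this for one participant in five. The headline estimate would then describe those who were measured at PT. It carries over to all 200 randomised only under a strong assumption about why the others were not measured.

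The protocol gives reason not to take that assumption for granted, because the arms ask and offer different things before PT. EUC has five weekly classes. FoRKS has those five, then two a week in weeks 6 to 12 and one a week in weeks 13 to 16, which is up to 7 × 2 + 4 = 18 more. EUC receives a weekly $10 gift card from week 6, whereas FoRKS gift cards start in week 17. FoRKS receives ingredient kits, kitchen tools and a tablet. Missingness at PT may therefore differ between arms in amount or in kind.

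An analysis that uses more of the data and needs a weaker assumption is already in the plan, but it is ranked second.

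**Working it through.** **1. Reproduce the power figure.** Inputs from Power and Sample Size: difference 6 mm Hg, SD 12 mm Hg, two-sided 0.05, 100 per arm randomised, 80 per arm at PT.

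- Formula: power ≈ Φ(Δ / (SD·√(2/n)) − 1.96).
- n = 80: standard error 12·√(2/80) = 1.90; 6/1.90 = 3.16; power = Φ(1.20) = 88.5%. The exact noncentral t with 158 df gives 88.2%.
- n = 100: standard error 12·√(2/100) = 1.70; 6/1.70 = 3.54; power = Φ(1.58) = 94.2%. The exact t gives 94.0%.
- Attrition: 80/(1 − 0.20) = 100, so the inflation is correct.

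The stated 88% matches 80 per arm and does not match 100. The plan therefore counts on information from about 160 of the 200 randomised.

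**2. What the observed-case difference estimates.** Let p be the fraction missing at PT in an arm, and g the mean PT SBP of the missing minus that of the observed. The mean for everyone in that arm is the observed mean + p·g. Hence

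bias (observed-case difference minus all-randomised difference, FoRKS − EUC) = p_EUC·g_EUC − p_FoRKS·g_FoRKS.

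This is zero if g = 0 in both arms (missingness unrelated to SBP within arm), or if the two products happen to be equal.

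**3. Possible size.** The protocol gives no value of g and no attrition by arm, so every line here is an assumption.

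| Assumed missing (FoRKS / EUC) | Assumed g | Bias |
|---|---|---|
| 20% / 20% | same in both arms | 0 |
| 20% / 20% | 5 to 10 mm Hg larger in one arm | 0.20 × 5 = 1.0 to 0.20 × 10 = 2.0 mm Hg, either direction |
| 25% / 15% | 6 mm Hg in both | 0.9 − 1.5 = −0.6 mm Hg (favours FoRKS) |
| 15% / 25% | 6 mm Hg in both | 1.5 − 0.9 = +0.6 mm Hg (favours EUC) |

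Against the standard error of 1.90 mm Hg, 0.6 is about 0.3 standard errors, and 1 to 2 is about 0.5 to 1.1.

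**4. What the planned model would use instead.** The sequence in Study Design puts the BL assessment before treatment assignment, so everyone randomised should have a baseline BP. Many who miss PT will also have a week-5 reading, and some an FU reading. A likelihood-based model keeps all of them. It needs missingness to be unrelated to the unseen PT value only after taking account of arm and the BP values that were observed. Including baseline also reduces the residual variance of the PT contrast, by a factor of roughly 1 − ρ², where ρ is the baseline-to-PT correlation. The protocol gives no ρ, so no figure is put on the gain.

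**The case against.** The strongest reply has four parts.

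- **The arms are analysed as randomised.** Intention-to-treat is set against a separate per-protocol analysis. Assessments can be done at home or in the clinic within a window of weeks 15 to 18, and payment is per assessment rather than per class. All of this stands. A reader might infer that the t-test estimates an effect only in people who complete the programme, more so given the full-dose wording. The documents do not support that: someone who stops attending but is measured at PT remains in the analysis.
- **A comparison of two means can be run after imputation, and powering on 80 is an ordinary attrition allowance.** This partly stands. The power figure alone does not rule out imputation, and a missing-data rule may sit in an analysis plan that is not at hand. The absence of such a rule is not the point. The point is that the protocol fixes an unadjusted PT-only comparison as the main analysis and makes the model that uses the other visits secondary.
- **The direction of bias is unknown.** This stands. A reader might infer from the class burden that the result will flatter FoRKS. Kits, tools and a tablet could equally hold people in FoRKS, and the protocol assumes 20% attrition overall without any difference between arms.
- **The mixed model does not cure every kind of dropout.** This stands too. Suppose the 20% without a PT value had no benefit: the effect in all randomised would be 0.8 × 6 + 0.2 × 0 = 4.8 mm Hg. If earlier BP does not predict that loss, the mixed model would still return about 6. Week-5 BP is also of limited help here, because both arms follow the same class curriculum up to week 5 and cooking starts in week 6. A reader might also set 4.8 against the 5.0 mm Hg in the aims. That comparison carries no weight, since 5.0 is a hypothesised effect and not a success threshold, and the zero benefit is an assumption.

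**Conclusion.** The point holds as a mismatch between the stated principle and the chosen primary method. The PT t-test is an observed-case analysis by randomised arm, planned on about 80% of participants. Carrying its result over to all randomised requires that missing PT values be unrelated to SBP within arm, or that any selection cancel between arms. A less demanding and probably more precise analysis is already planned on data already collected.

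What is shown is a restricted analysis set and an avoidable assumption, not a proven bias. The illustrations of 0.6 to 2 mm Hg rest on assumed attrition and assumed differences between missing and observed participants, and they can go either way. The conclusion takes the protocol text as it stands. If a separate analysis plan specifies imputation for the primary test, the missing-data part weakens, but the case for using baseline remains. The change should be made before any comparison by arm is seen.

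**What to change.** 1. Make the repeated-measures model of SBP the primary analysis, with arm-by-visit terms, a common baseline mean and a covariance structure named in advance. Take the FoRKS − EUC contrast at PT as the primary estimate, using all randomised participants with any BP value.
2. State whether the primary SBP is the Omron or the ABPM reading. The four-visit model (BL, week 5, PT, FU) fits the Omron schedule. If ABPM is primary, use the same baseline-adjusted model on its two occasions, EV and PT.
3. Keep the t-test as a supportive analysis and describe it as observed-case.
4. Add one delta-adjusted sensitivity analysis, shifting the missing PT values by a range of amounts and allowing the shift to differ by arm. The mixed model does not protect against dropout that depends on the unseen value.

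The cost is a re-ranking of planned analyses with a fuller model specification, plus one sensitivity analysis. No new data and no change in sample size are needed. The downside is slightly more analysis work and a primary estimate that depends on a model rather than on a simple difference of two means.

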EUC consists of SDOH screening, referrals to food pantries, assistance enrolling in food programs (e.g., SNAP), and access to CDC-approved HTN Self-Management Education Series (SMES) and, if applicable, DM2 SMES. *In addition to the EUC offerings*, participants randomized to FoRKS will receive home-delivered ingredient kits and Webex cooking classes with embedded lessons in kitchen organization, tool use, nutrition, budgeting, and shopping.

Specific Aims and Hypotheses:

1. **Primary Aim.** Determine the effects of FoRKS on disease management.

Effectiveness Hypothesis: Compared to EUC at PT, FoRKS participants will have lower mean systolic blood pressure (SPB) (-5.0 mm Hg). Among those with both DM2, we will secondarily examine FoRKS’ effect in lowering HbA_1c_.

1. **Intervention Processes**. Identify behavior change levers and their associations with change in food security, nutrition, and SBP.

Intervention Process Hypotheses: 2.1) FoRKS participants will report greater food-related social support and self-efficacy, and food management skills at PT and 2.2) these gains will partially account for better food security, nutrition, and SBP relative to EUC. 2.3) Higher learning engagement will be associated with greater social support, self-efficacy, and food skill gains among FoRKS participants.

1. **Maintenance.** From PT to FU, determine the percent of FoRKS versus EUC participants who maintain improved food security, nutrition, and SPB (and/or HbA_1c_ if applicable).
2. **Reach and Cost.** Assess reach and intervention cost-effectiveness in preliminary economic analyses.
3. **Eligibility Criteria**

The target population is midlife adults aged 35-75 years with normal cognition, food insecurity, and a recent systolic BP ≥120 mm Hg.

We will enroll only one individual per household.

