For recruitment methods #1-3, patients passing the telephone screen will be invited to schedule an Eligibility Visit for informed consent and 24-hour ABPM initiation. After 24 hours, patients who meet criteria for ABPM will be asked to complete the Baseline (BL) assessment, including all other outcome measures described in Section 5.

For recruitment method #4, ABPM from FoRKS+ eligibility visit will be used to satisfy FoRKS ABPM inclusion criteria for patients meeting eligibility criteria and consenting to the study.

Treatment assignment will occur prior to intervention for all participants in the replicate; block-4 randomization will be used to ensure equal groups. Target randomization is n=200. Randomization will be stratified by race (i.e., Black/all others), sex (male/female), and DM2 status (i.e., DM2 yes/no) to minimize imbalance in treatment assignments in key subgroups. [Participants who are randomized but are unable to start intervention in their replicate due to changes in health status, schedule availability, etc, will be allowed to participate in the immediately subsequent replicate with the same treatment assignment; ABPM and BL assessment will not be repeated. If participant wants to postpone participation until later replicates, ABPM and BL assessment will be repeated.]

Prior to intervention start, all participants will complete a 1-on-1 consult with an Eskenazi dietician to complete an enrollment appointment for Hypertension group. This consult may be completed at an Eskenazi health center or via phone, and take 30-60 minutes to complete.

Intervention will be conducted in replicates targeting 20 participants (+/- 8 participants) with 10 in each arm (+/-4 participants). A Post-training (PT) assessment will be conducted near Week 16 as the primary endpoint, and Follow-Up (FU) assessment will be conducted around Week 24 for data on maintenance of PT outcomes. Adverse events will be recorded any time they become known to study staff.

1. **Intervention**

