**Mood and Health-Related Quality of Life.** We will include the PHQ-8 and Generalized Anxiety Disorder measures, as well as the EQ-5D-5L health outcomes questionnaire. Participants scoring ≥ 12 on PHQ-8 or > 15 on GAD-7 will be instructed to contact their PCP and notified that the internal safety officer will also alert the participant’s PCP of their high score.

**Blood Pressure & Pulse (BL, PT, FU, and post SMES).** We will measure BP and pulse using standard procedures with an Omron series 10 device and calculate pulse pressure (i.e., the difference between systolic and diastolic BP). Blood pressure will be measured 3 times at each assessment.

**ABPM (EV and PT).** We will also measure 24-hour blood pressure using the Spacelabs Healthcare ambulatory blood pressure monitor (ABPM), once at Eligibility Visit and once at PT. Appropriately sized cuffs will be used with bladder sizes that encircle 80–100% of arm circumference and widths that are at least 40% of arm circumference. We will measure ambulatory BP three times per hour during participant’s normal daytime hours and two times per hour during participant’s normal nighttime (i.e., sleep) hours. Resting heart rate is recorded by the Spacelabs device.

**HbA_1c_ (BL, PT, FU).** We will measure HbA1c with 1 μL of whole-blood from a fingerstick using a point-of-care analyzer at each assessment. Manufacturer operation guidelines will be followed for obtaining and analyzing samples. HbA1c values will be shared with participants.  Any participant who has an HbA1c value above 6.5% will be given a recommendation to communicate with their PCP.  For any participant with a value above 9%, our internal safety officer will share the value and collection method directly with the PCP as well.

Any participant who had venous whole blood collection prior to this protocol change will have blood collected at each remaining visit in their schedule of events. For these participants, phlebotomists will draw the blood, mix by inversion 4-5 times, then freeze on dry ice for transport to the laboratory. Specimens will be stored at -80°C until the time of assay. HbA_1c_ measures will be performed in the Analyte Lab ([name] Laboratory) at the Center for Diabetes and Metabolic Diseases at Indiana University.

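### The primary t-test on post-training SBP is valid and correctly powered, but it leaves out baseline SBP and the randomisation strata, so it is less efficient than a pre-specified adjusted analysis

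*Protocol*

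**What the plan says.** Under Statistical Considerations (Analytic Plan, Primary Aim) the protocol fixes the main analysis: "Mean SBP at PT will be compared between the two treatment groups using a t-test". HbA1c is to be compared by the same test. The power paragraph sizes the trial for this comparison, "with a two-sided t-test at 0.05 significance level", and names no covariate.

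Two kinds of pre-treatment information are available:

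- **Baseline SBP.** Measures and Outcomes lists the office (Omron) reading at BL and PT, and the 24-hour ambulatory reading at the Eligibility Visit and PT. Both methods therefore give a value before treatment and one at the primary endpoint.
- **Strata.** Study Design states: "Randomization will be stratified by race (i.e., Black/all others), sex (male/female), and DM2 status (i.e., DM2 yes/no".

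Mixed-effect models of the repeated BP readings, including BL, are planned in addition to the main analysis. Their role in adjustment is described thus: "These secondary analyses will allow us to control the effects of any participant characteristics that are not balanced". The strata are not named as terms in any model.

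**The concern.** Baseline SBP is usually a natural covariate for later SBP. An unadjusted comparison of PT means costs precision in two related ways. Variation between people that their baseline would explain remains in the error term. Any chance difference in baseline SBP between the arms passes partly into the estimated effect.

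Leaving the strata out means that the analysis does not match the randomisation. The t-test's standard error then does not credit the balance that stratification creates.

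In the secondary models, tying adjustment to characteristics that turn out unbalanced would make the covariates depend on the data. It could also pass over a prognostic variable that happens to look balanced.

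At stake is the chance of detecting the hypothesised effect and the width of its confidence interval, with data the trial already collects.

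**Working it through.** **Inputs from the protocol (Power and Sample Size, unless noted).** 80 per arm at PT (100 randomised, 20% attrition); two-sided alpha 0.05; stated power 88%; SD from "Using a conservative estimate of the SD of 12 mm Hg"; effect from "FoRKS participants will have lower SBP (-6.0 mm Hg) at PT". The Specific Aims give a different effect: "FoRKS participants will have lower mean systolic blood pressure (SPB) (-5.0 mm Hg". Both effects are carried through.

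**Assumptions not in the protocol.** (a) The SD of 12 is the SD of SBP at PT; the text does not say whether it refers to PT values, change or residuals. (b) The baseline-to-PT correlation r lies between 0.3 and 0.7.

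**Step 1: the protocol's own figure.** The standard error of the difference is 12 × √(2/80) = 1.90 mm Hg, so the standardised effect is 6/1.90 = 3.16. The normal approximation gives 88.5%, and the noncentral t with 158 degrees of freedom gives 88.2%. The stated 88% reproduces. At 5 mm Hg the same test has 74.5% power.

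**Step 2: adjust for baseline SBP.** Residual SD = 12 × √(1 − r²); noncentral t with 157 degrees of freedom; equivalent unadjusted completers per arm = 80/(1 − r²).

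| r | Residual SD | Power at 6 mm Hg | Power at 5 mm Hg | Equivalent completers per arm |
|---|---|---|---|---|
| unadjusted | 12.0 | 88.2% | 74.5% | 80 |
| 0.3 | 11.4 | 90.9% | 78.4% | 88 |
| 0.4 | 11.0 | 92.9% | 81.5% | 95 |
| 0.5 | 10.4 | 95.2% | 85.6% | 107 |
| 0.6 | 9.6 | 97.5% | 90.6% | 125 |
| 0.7 | 8.6 | 99.3% | 95.6% | 157 |

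The gain is about 3 to 11 points at 6 mm Hg and about 4 to 21 points at 5 mm Hg. The variance saved is r², that is 9% to 49%.

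**Step 3: chance imbalance.** If the baseline SD is also 12 (assumed), the baseline difference between arms of 80 has a standard error of 1.90 mm Hg and a 95% range of about ±1.96 × 1.90 = ±3.7 mm Hg. At r = 0.5 about half of that, ±1.9 mm Hg, carries into the unadjusted estimate. This is the Step 2 loss seen from another side, not an additional one.

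**Step 4: strata alone.** The share of SBP variance explained by race, sex and DM2 is not given. If it is 2%, 5% or 10%, power at 6 mm Hg becomes 88.8%, 89.7% or 91.2%, a gain of about 0.6 to 3 points. With the strata balanced by design and then ignored, the actual two-sided error rate is approximately 2 × [1 − Φ(1.96/√(1 − share))], which gives 0.048, 0.044 and 0.039. The unadjusted test is slightly conservative.

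**The case against.** The strongest reply is that this is a preference about efficiency and not an error. Under 1:1 randomisation the t-test is unbiased, it is the test the trial was sized for, and the power claim is right. All of that stands.

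Four stronger readings are tempting, and the protocol does not support them.

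- **That the power loss is substantial.** This depends on a correlation the protocol never gives. At 6 mm Hg and r = 0.3 the gain is only about 3 points. Entry requires a mean ambulatory SBP of at least 120, and truncating the baseline range tends to lower the correlation, so low values cannot be ruled out. If 12 is already a change or residual SD, the adjusted powers above are too high; but then the 88% would not describe a t-test on PT values. The larger gains occur at 5 mm Hg and so borrow from a separate inconsistency over the target effect.
- **That the primary result is open to covariate picking.** The primary t-test has no covariates to pick. The sentence on unbalanced characteristics concerns secondary models, says what they allow and sets no selection rule. Those models already use baseline BP, and a covariate list may properly sit in an SAP.
- **That mixing HbA1c collection methods biases the arm comparison.** The protocol says: "Any participant who had venous whole blood collection prior to this protocol change will have blood collected at each remaining visit". These participants thus stay on the venous method. The method depends on when a person entered, and both arms are randomised within each replicate. No bias between arms is shown.
- **That deferral settles which baseline to use.** Study Design repeats the ambulatory and BL measurements for participants who postpone to later replicates, but does not say whether they keep their assignment. No rule for their baseline can be derived from that text.

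The objection therefore limits the size and tone of the point. It gives no reason to prefer the unadjusted test as primary.

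**Conclusion.** The point holds as a recommendation to improve efficiency. The primary analysis is valid and its 88% is correct, but it omits baseline SBP and the strata that the trial already holds. It is therefore less precise than an adjusted analysis whenever baseline SBP has a useful correlation with SBP at PT.

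Under the two stated assumptions the benefit is modest to moderate at the planning effect of 6 mm Hg. It matters more at 5 mm Hg, where the unadjusted test falls below 80% and adjustment passes 80% at r of about 0.4. The case for the strata rests on matching analysis to design and on avoiding slight conservatism, not on power. Confidence is high that adjustment is the better choice and lower on how much it gains.

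**What to change.** In the Analytic Plan, Primary Aim:

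1. Make the primary analysis a pre-specified ANCOVA, or a baseline-constrained mixed model, of PT SBP on arm. Adjust for pre-randomisation SBP measured by the same method as the primary SBP outcome, and for race, sex and DM2 status as randomised. The text must therefore say whether the primary SBP is the office or the ambulatory reading.
2. Keep the t-test as a supportive analysis.
3. Name the covariates of the secondary models in advance, in place of adjustment for observed imbalance.
4. Analyse HbA1c in the same way, with its baseline value as a covariate.
5. State in the power paragraph which SD the 12 mm Hg is. The sample size need not change.

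The cost is analysis wording and a few degrees of freedom. No new data are needed, and a mixed model that uses baseline BP is already planned.
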